#### Relevant concomitant care and interventions that are permitted or prohibited during the trial {11d}

##### Concomitant therapy

Pre-study therapies administered up to 30 days prior to administration of the first dose of a study intervention must be recorded at the time of screening. Concomitant therapies must be recorded throughout the study from the time of initiation of the first study intervention dose.

All therapies, including prescription or over-the-counter medications (e.g., vaccines, vitamins, and herbal supplements) and non-pharmacologic therapies (e.g., electrical stimulation, acupuncture, special diets, exercise regimens, or other specific categories of interest) that differ from study interventions, must be recorded in the CRFs. Recorded information will include a description of the type of therapy, duration of use, dosing regimen, route of administration, and indication. Modification of an effective preexisting therapy should not be made for the explicit purpose of entering a participant into the study.

##### Prohibited medications

The use of the following drugs is not permitted concomitantly with BDQ administration through day 30 after administration of the last dose of BDQ:Systemic use of moderate and strong cytochrome P450 3A4 (CYP3A4) inhibitors for more than three consecutive days.Systemic use of moderate or strong CYP3A4 inducers.Medications of the statin class of compounds.Tricyclic antidepressants, including amitriptyline, doxepin, desipramine, imipramine, and clomipramine.Nonsedating antihistamines astemizole and terfenadine.Phenothiazine neuroleptic drugs thioridazine, haloperidol, chlorpromazine, trifluoperazine, percycline, prochlorperazine, fluphenazine, sertindole, and pimozide.The prokinetic drug cisapride.Quinoline antimalarials and quinolones used for other indications.Gatifloxacin and MFX.

#### Provisions for post-trial care {30}

If a participant discontinues a study intervention for any reason before the end of the study treatment period, end-of-intervention and post-intervention assessments will be conducted and scheduled study intervention assessments will continue during the 48-week follow-up phase, as outlined in the protocol. Participants who discontinue treatment are encouraged to complete quarterly visits for 1 year as per the protocol schedule unless they withdraw informed consent. Documentation of assessment results obtained after treatment discontinuation is encouraged. Based on patient treatment responses, investigators will formulate and administer more suitable new treatment regimens as needed. Investigational drugs will not be incorporated into new treatment regimens administered to patients.

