## Trial design {8}

This is an open-label, parallel-group, randomized, controlled, multicenter, interventional, pragmatic, phase 4, clinical study that assesses non-inferiority. The study aims to assess the efficacy and safety of an oral BDQ-containing SCR as compared to corresponding performance indicators of an oral SCR without BDQ. Our goal is to enroll a total of 212 participants (106 participants/regimen) aged 18 to 65 years with microbiologically confirmed pulmonary MDR-TB. The study will be implemented within the framework of the China Tuberculosis Clinical Trial Consortium (CTCTC) network [19].

The PROSPECT study process consists of a screening phase of up to 8 weeks, a study treatment phase of 40 weeks, and a 48-week follow-up phase occurring after treatment completion. Monitoring of all recruited participants will be conducted for 88 weeks post-randomization after completion of the screening phase. A diagram outlining the study design is provided in Fig. 1.

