#### Criteria for discontinuing or modifying allocated interventions {11b}

A participant’s study intervention must be discontinued if:The participant withdraws consent to receive the study intervention.The investigator believes that for safety or tolerability reasons it is in the best interest of the participant to discontinue the study intervention. Individual drug substitutions within the study intervention regimen may be considered if clinically indicated at the discretion of the investigator. Administration of single-drug substitutions will not be viewed as an unfavorable treatment outcome criterion if limited to substitutions of non-group A drugs (except DLM) as per the 2020 WHO MDR-TB treatment guidelines.The participant becomes pregnant.Unacceptable toxicity.The patient experiences:Aminotransferase elevations with total bilirubin elevations to levels of ≥ twofold the ULNAminotransferase elevations to levels that are ≥ eightfold greater than the ULNAminotransferase elevations to levels that are ≥ fivefold greater than the ULN and persist for more than 2 weeks.If the patient experiences a QTcF interval > 500 ms (as confirmed by repeat ECG) and/or clinically significant ventricular arrhythmia.Noncompliance with study drug administration.Any participant not meeting eligibility criteria as specified in the “Eligibility criteria” section.

A participant will be withdrawn from the study for any of the following reasons:If phenotypic DST results from a screening sample become available post-baseline confirming resistance at the start of the study to any of the drugs in the assigned regimen except BDQ, in which case the patient will be treated according to local treatment protocols after withdrawal from the study.Lost to follow-up.Withdrawal of consent.Death.

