#### Secondary outcomes

Proportion of participants with a favorable treatment outcome at 48 weeks post-treatment completion.Proportion of participants achieving treatment success at treatment completion (week 40).Proportion of participants experiencing mortality from all causes.Proportion of participants experiencing grade 3 or greater treatment-emergent adverse events (TEAEs) during study treatment and follow-up phases.Proportion of participants experiencing TEAEs of all types.Proportion of participants with a modified favorable treatment outcome at treatment completion and 48 weeks post-treatment completion.Proportion of participants with TB relapses and re-infections during the post-treatment follow-up phase.Proportion of participants harboring *MTB* that develops resistance to BDQ and other drugs included in the regimen.

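### Follow-up after stopping treatment is required in one place and only encouraged in another, and late-found baseline resistance ends it under an arm-dependent rule, so mortality, adverse-event and acquired-resistance data can be incomplete and unequal between arms

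*Protocol article*

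**What the plan says.** All references are to the protocol article.

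- **Trial design {8}** sets "a study treatment phase of 40 weeks, and a 48-week follow-up phase occurring after treatment completion" and states without exception: "Monitoring of all recruited participants will be conducted for 88 weeks post-randomization after completion of the screening phase".
- **Provisions for post-trial care {30}** opens with a requirement. For anyone stopping the intervention early, whatever the reason, end-of-intervention and post-intervention assessments are to be done and "scheduled study intervention assessments will continue during the 48-week follow-up phase, as outlined in the protocol".
- **The same section** then changes register: "Participants who discontinue treatment are encouraged to complete quarterly visits for 1 year as per the protocol schedule unless they withdraw informed consent". It adds: "Documentation of assessment results obtained after treatment discontinuation is encouraged".
- **Criteria for discontinuing or modifying allocated interventions {11b}** keeps two lists, one for stopping the intervention and one for leaving the study. The second begins "A participant will be withdrawn from the study for any of the following reasons". Its first entry is phenotypic resistance in the screening sample, reported after baseline, to a drug of the assigned regimen other than bedaquiline. In that case "the patient will be treated according to local treatment protocols after withdrawal from the study".
- **Table 3** removes these resistance cases from the modified ITT and efficacy sets. The ITT set (all randomized) and the safety set (all randomized and dosed) keep them.
- **Secondary outcomes** include "Proportion of participants experiencing mortality from all causes", grade 3 or greater TEAEs over the treatment and follow-up phases, any TEAE, and acquired resistance, all as proportions of participants.

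**The concern.** A site that reads section {8} must follow a participant who stops at week 8 until week 88. A site that reads the later sentences of section {30} may treat both the visits and their documentation as voluntary. Both sites would be following the protocol.

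The outcomes exposed are those expressed as proportions of participants over the whole study period. Such proportions compare fairly only if both arms are observed for similar time. Section {22} collects adverse events up to each participant's last study procedure, so the adverse-event window shrinks whenever that participant's follow-up does.

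Resistance withdrawals add a second problem. The protocol itself ends their observation while they remain in the ITT and safety denominators, and the trigger is not the same in the two arms. In an open-label comparison of safety and mortality, the end of observation should not depend on the assigned regimen.

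**Working it through.** **1. The plan's own figure.** 40 weeks of treatment + 48 weeks of follow-up = 88 weeks, as section {8} states. Table 1 places the follow-up visits at weeks 52, 64, 76 and 88, each 12 weeks apart. The planned schedule is consistent for a participant who completes treatment.

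**2. Required or optional.** Section {8} (all participants) and the first sentence of section {30} (any reason for stopping) are mandatory. The second and third sentences of section {30} only encourage attendance and documentation. This conflict exists however the year is counted.

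**3. Nominal weeks lost, stopping at week s.** The start of the year is not stated, so there are two readings.

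- *Scheduled visits (weeks 52 to 88):* observation nominally ends at week 88, so the loss is 0.
- *Year from the stop date:* the loss is 88 − (s + 48) = 40 − s weeks if the year is the 48-week phase, or 88 − (s + 52) = 36 − s weeks if it is 52 weeks (never below 0).

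| Stop at week s | Loss, scheduled visits | Loss, 48 weeks from stop | Loss, 52 weeks from stop |
|---|---|---|---|
| 8 | 0 | 32 (36% of 88) | 28 (32%) |
| 16 | 0 | 24 (27%) | 20 (23%) |
| 24 | 0 | 16 (18%) | 12 (14%) |
| 40 | 0 | 0 | 0 |

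**4. Resistance withdrawals.** No follow-up is described after withdrawal from the study, so a withdrawal at week s loses 88 − s weeks: for example 88 − 8 = 80, or 88 − 16 = 72. The article does not say when the phenotypic results arrive, so these values of s are illustrations.

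**5. Arm dependence of that withdrawal.** Set Table 2 beside the screening phenotypic DST list in section {33}:

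- Levofloxacin, linezolid and clofazimine are in both regimens and on the list. The rule is the same in both arms.
- Bedaquiline is in the experimental regimen only and on the list, but section {11b} exempts it.
- Prothionamide is in the control regimen only, is on the list and is not exempt.
- Pyrazinamide is also control-only and not exempt, but it is not on the list.

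So late-found prothionamide resistance ends observation for a control participant and not for an otherwise identical participant in the bedaquiline arm. No tested drug has the reverse effect. The article gives no frequency for late-found prothionamide resistance, so the imbalance cannot be sized.

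**6. Which outcomes are touched.** Under Primary outcomes, treatment discontinuation is itself unfavorable, so a stopper's primary outcome is already decided. Resistance withdrawals are outside the efficacy set used for the primary analysis. The week-88 favorable outcome is very probably settled in the same way, assuming the unfavorable classification carries forward. That leaves mortality, TEAEs and acquired resistance.

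**The case against.** The best defence is that section {30} is loosely worded but sound. Quarterly visits on the protocol schedule match weeks 52, 64, 76 and 88, so the natural reading costs no weeks. Section {22} requires every adverse event to be documented, follow-up of events to resolution or improvement, and serious events to be reported within 24 hours. Section {18b} requires active contact after missed visits. Encouraging attendance may only reflect that participation is voluntary. The full protocol may also fix the timing.

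Much of this stands, and it rules out several stronger readings that a reader might infer:

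- *That early stoppers as a group get no follow-up.* The study-withdrawal list is separate. Death, loss to follow-up and withdrawn consent end observation in any trial. Only the resistance entry clashes with the any-reason wording of section {30}.
- *That follow-up of all stoppers is certainly shortened.* This holds only if the year runs from the stop date.
- *That nothing happens between the stop and week 52.* End-of-intervention and post-intervention assessments are required, though the article does not give their timing.
- *That 25% to 40% of later deaths would be missed.* Those are shares of post-stop time (16/64, 24/72 and 32/80 for stops at weeks 24, 16 and 8). They become shares of deaths only under the 48-week stop-date reading, no observation afterwards and an assumed constant hazard.
- *That stoppers are the highest-risk participants, or that the arm with more stopping must look safer.* The first is plausible, but the article gives no figure for it. The second does not follow for someone who stops because of a grade 3 event, who is already counted.

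What the defence does not remove is the clash between required and encouraged within one section, or the protocol-imposed end of observation for resistance cases. Section {22} does not help after withdrawal, because its reporting window closes with the participant's final study procedure. It is also true that later events on local treatment say less about the allocated regimens, but those participants still count in the ITT and safety denominators. These are conflicting statements rather than detail left to a fuller document, and no analysis plan can recover data that sites were told were optional.

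**Conclusion.** The point holds as a contradiction between sections {8}, {11b} and {30} that should be reconciled. It concerns secondary outcomes: all-cause mortality, TEAEs through follow-up and acquired resistance. The sample size is not touched.

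Early end of observation is certain only for participants withdrawn for late-found baseline resistance, who lose all remaining weeks (88 − s) under a rule that can remove more control than experimental participants. For other stoppers the certain defect is that attendance and documentation are optional. The nominal loss ranges from 0 to 40 − s weeks depending on the reading. The effect on the outcome proportions cannot be estimated, because the article gives neither the number of stoppers or resistance withdrawals by arm nor their event rates.

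**What to change.** Write one data-collection rule and use it in sections {8}, {11b} and {30}. Anyone who stops study treatment, including for late-found baseline resistance, stays on the randomization calendar to week 88. Vital status and adverse events are required rather than encouraged, with cultures at the existing Table 1 visits where feasible. Required collection ends early only on death or when consent to follow-up is withdrawn. For resistance cases, separate ending study treatment from ending data collection, so that observation no longer depends on the assigned regimen.

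The cost is protocol wording and some site effort to follow participants treated elsewhere. Trial status places the end of recruitment in early 2024, so 88-week follow-up of the last participants runs well past the article's publication and the clarification could still take effect. No change to treatment or to the stopping criteria is proposed.

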### Outcomes {12}

#### Primary outcomes

The primary outcome is the proportion of participants with a favorable treatment outcome at treatment completion (week 40). In this work, patient outcomes will be classified as favorable if their last three culture results prior to treatment completion are negative, unless they had previously been classified as unfavorable. These three cultures must be taken on separate visits, the latest of which will be taken no more than 8 weeks prior to the treatment completion date. Unfavorable outcomes include the following: treatment discontinuation; starting 2 or more drugs not in the allocated regimen; treatment continuation beyond the permitted duration; death; lost to follow-up prior to treatment completion; relapse and re-infection. Treatment success is achieved if participants completed their prescribed TB treatment or if their last three culture results by the end of treatment are negative (these 3 cultures must be taken on separate visits).

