### Secondary objectives

To compare favorable treatment outcomes of an all-oral BDQ-containing SCR versus those of an all-oral SCR without BDQ at 48 weeks post-treatment completion in participants with pulmonary MDR-TB in China.To evaluate efficacy based on treatment success of an all-oral BDQ-containing SCR versus an all-oral SCR without BDQ at treatment completion in participants with pulmonary MDR-TB in China.To evaluate the safety of an all-oral BDQ-containing SCR versus that of an all-oral SCR without BDQ in participants with pulmonary MDR-TB in China.To evaluate modified favorable treatment outcomes associated with the administration of an all-oral BDQ-containing SCR versus outcomes of an all-oral SCR without BDQ at treatment completion and at 48 weeks post-treatment completion in participants with pulmonary MDR-TB in China.To evaluate TB relapse and re-infection rates during the post-treatment follow-up phase in participants with pulmonary MDR-TB in China.To evaluate rates of emerging resistance to BDQ and other anti-TB drugs incorporated within the all-oral SCR with and without BDQ regimen used to treat participants with pulmonary MDR-TB in China.

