### Plans for collection, laboratory evaluation, and storage of biological specimens for genetic or molecular analysis in this trial/future use {33}

Three sputum samples will be collected from each participant at pre-scheduled visits, as detailed in Table 1; these samples will include one sample taken at night, one collected early the next morning, and one coached spot expectoration sample. While awaiting receipt of phenotypic DST results, participant *MTB* isolates will be screened for RMP resistance using GeneXpert, while other molecular DST methods will be used to screen for FQs resistance and INH resistance-associated *inhA* and *katG* mutations. Participants harboring *MTB* with susceptibility to RMP and INH, FQ resistance, or *inhA* mutation-induced INH resistance will be excluded from the trial. Participants harboring *MTB* with RMP resistance, INH sensitivity, or high-level INH resistance due to *KatG* mutations and FQs susceptibility, as confirmed using molecular methods, may be enrolled in the study while awaiting phenotypic DST results.

MGIT-based DST will be performed on cultures derived from specimens obtained at baseline, during treatment, and during the follow-up period. Phenotypic DST will be performed during the screening phase to detect resistance to RMP, INH, LFX, LZD, CFZ, PTO, and BDQ. If sputum cultures obtained at screening test positive for drug resistance within 1 month prior to the date of administration of the first dose of the study regimen, the culture obtained at screening may serve as the baseline culture. Post-baseline cultures of specimens collected from participants during or after week 16 of treatment that test positive for *MTB* will be stored until assayed via DST. DST will also be performed on any *MTB*-positive culture derived from specimens obtained during the follow-up period. Cultures obtained from specimens collected during the follow-up period from participants with treatment success who later revert to *MTB*-positive status (as indicated by culture conversion or disease relapse) will be genotyped, with paired *MTB*-positive isolates used for genotypic analysis.

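### The secondary outcome of treatment success is met by completing treatment or by three negative cultures, so culture-positive completers and some non-completers count as successes

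*Protocol article*

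**What the plan says.** The definition stands at the end of the Primary outcomes paragraph in Outcomes {12}: "Treatment success is achieved if participants completed their prescribed TB treatment or if their last three culture results" up to the end of treatment are all negative, with a note that the three cultures come from separate visits.

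Treatment success is not the primary outcome. It is a secondary objective ("To evaluate efficacy based on treatment success of an all-oral BDQ-containing SCR versus an all-oral SCR without BDQ at treatment completion") and a secondary outcome ("Proportion of participants achieving treatment success at treatment completion (week 40"). Statistical methods {20a} gives secondary outcomes the same stratified risk difference as the primary endpoint, with point estimates and confidence intervals. It states no margin for them.

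The primary outcome is defined separately in the same paragraph. A participant is "classified as favorable if their last three culture results prior to treatment completion are negative, unless they had previously been classified as unfavorable", and the latest of the three cultures must fall within 8 weeks before completion. The unfavorable list includes "treatment discontinuation; starting 2 or more drugs not in the allocated regimen; treatment continuation beyond the permitted duration; death; lost to follow-up" before completion, then relapse and re-infection.

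The term appears again in the biological specimens section {33}, where follow-up cultures are genotyped for "participants with treatment success who later revert to" a positive status.

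**The concern.** Two criteria joined by *or* are each sufficient. Completion carries no culture condition, and negative cultures carry no completion condition. A participant can therefore be a bacteriological failure and a treatment success, or be unfavorable on the primary outcome because treatment stopped and still be a success here.

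At stake is the meaning of a named efficacy outcome in an open-label trial intended to inform practice. As written, the success rate is partly a completion rate. If the arms differ in how many participants finish treatment while still culture-positive, the comparison will understate that difference, and a reader of the results would not know.

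**Working it through.** **1. The plan's own figure.** The point rests on no figure in the article. The one relevant calculation, the sample size, belongs to the primary outcome and can be reproduced. Inputs from Sample size {14}: control rate 85%, margin 15 points, one-sided 0.025, power 80%, 10% not evaluable. A true rate of 85% in the bedaquiline arm is my assumption. The Farrington–Manning score method has null-restricted rates of 0.7489 and 0.8989:

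n = [1.960·√(0.7489·0.2511 + 0.8989·0.1011) + 0.8416·√(2·0.85·0.15)]² / 0.15² = 94.76, so 95 per arm.

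95 / 0.9 = 105.6, so 106 per arm and 212 in total, as printed. Treatment success does not enter this calculation.

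**2. The definition as a truth table.**

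| Completed treatment | Last three cultures | Treatment success as written | Primary favorable outcome |
|---|---|---|---|
| Yes | all negative | yes | yes, if timing is met and not already unfavorable |
| Yes | at least one positive | **yes** | no |
| No | all negative | **yes** | no |
| No | at least one positive | no | no |

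The two cells in bold are the problem.

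**3. Can those cells occur?**
- *Completed, culture-positive.* Under Intervention descriptions {11a}, a positive culture at week 16 extends bedaquiline in the experimental arm; it does not remove the participant. Section {11b} does not name a positive culture among its reasons for discontinuation or withdrawal. The unfavorable list has no culture-positive or failure item. Nothing in the article screens this participant out.
- *Not completed, three negative cultures.* Table 1 schedules cultures at weeks 12, 16 and 20, among other visits. Someone negative at those three visits who then stops, is lost or dies meets the second limb.

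**4. Conflict with section {33}.** Reverting to positive presupposes having been negative. The definition in Outcomes {12} does not guarantee that for a success, so the two sections use one term with two meanings.

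**5. Effect on the estimate.** In one arm, let c be the proportion completing, f the proportion completing with at least one positive among the last three cultures, and s the proportion not completing whose last three cultures were negative.

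- As written: success = c + s, which is never below c.
- Under the definition proposed below: success = c − f.
- Excess per arm = f + s.
- Bias in the between-arm difference = (f + s) in the bedaquiline arm minus (f + s) in the control arm.

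The documents give neither f nor s. For illustration only, take s = 0 and f = 2%, 5% or 10% of 95 evaluable participants: 95 × 0.02 = 1.9, 95 × 0.05 = 4.75 and 95 × 0.10 = 9.5, or about 2, 5 or 10 extra successes per arm. If f is equal in both arms, the difference is unchanged (5 − 5 = 0 points). If f were 2% in one arm and 10% in the other, the difference would shift by 10 − 2 = 8 points in favor of the arm with more culture-positive completers.

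**The case against.** The best defense is that the primary outcome is untouched. It requires three negative cultures and excludes anyone already unfavorable, and the hypothesis, margin and sample size rest on it alone. This stands, and it limits the point to one of several secondary outcomes.

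A second defense is that the authors meant completion without evidence of failure, and that section {33} shows they think of successes as culture-negative. That is plausible, and a reader should not infer an intention to count failures as successes. But the article prints a complete rule rather than omitting one, and a variable programmed from that text would give the wrong answer. That the article condenses a fuller protocol does not excuse a rule that it states in full.

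Three stronger readings are tempting but not supported:
- *The inflation uses up part of the 15-point margin.* That margin is set for the favorable outcome, and none is stated for treatment success. Moreover, inflation within an arm is not a shift between arms; equal inflation cancels.
- *Never-converted participants enter the relapse group.* Section {33} is a specimen-handling rule, sets no relapse denominator, and is triggered by reverting, which a never-negative participant cannot do. The relapse outcome under Secondary outcomes does not mention treatment success.
- *Success should carry every safeguard of the primary outcome.* That would nearly duplicate the primary outcome and leave the separate objective redundant. Leaving out the drug-change criteria may be deliberate and is not an error in itself.

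**Conclusion.** The definition is wrong as written, not merely short of detail. Taken literally, it counts culture-positive completers as successes, together with participants who stopped, were lost or died after three negative cultures, and it clashes with how section {33} uses the term. The effect is confined to the treatment-success objective and outcome at week 40, where an arm's rate cannot drop below its completion rate. The size cannot be computed from the documents; the 2%, 5% and 10% shares above are assumptions that show scale only. The between-arm difference is biased only to the extent that the misclassified shares differ between arms. The non-inferiority conclusion on the primary outcome does not depend on this.

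**What to change.** Replace the sentence in Outcomes {12} with a definition of this kind: treatment success is completion of the prescribed treatment with no positive result among the last three cultures by the end of treatment, these being from separate visits. Add that a participant who died, was lost or stopped treatment before completion is not a success on the strength of earlier negative cultures alone. Use the same definition in section {33}, so that those described as reverting were negative beforehand.

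The outcome remains distinct from the primary one: it need not take over the drug-change criteria, and it does not demand a full set of three negative results.

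The cost is a sentence of text and one reprogrammed derived variable. The cultures are already scheduled in Table 1, so no new data are needed. The downside is that reported success rates may be slightly lower.
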